# CHoosing Active Role Models to INspire Girls (CHARMING): protocol for a cluster randomised feasibility trial of a school-based, community-linked programme to increase physical activity levels in 9–10-year-old girls

**DOI:** 10.1186/s40814-021-00961-6

**Published:** 2022-01-03

**Keywords:** Physical activity, Children, Primary school

## Abstract

**Background:**

In the UK, there is evidence that girls’ physical activity tends to decline to a greater extent than boys as they enter adolescence. ‘Role models’ could play a vital role in inspiring girls to become or remain physically active. The CHARMING Programme is a primary school-based community linked role-model programme, co-developed in 2016, with children, parents, schools and wider stakeholders. It involves different types of physical activity delivered for 1-h each week by a community provider and peer role models (e.g. older girls from secondary schools) joining in with the sessions. The programme ultimately aims to increase and sustain physical activity levels among 9–10-year-old girls. This study aims to assess the feasibility and acceptability of the CHARMING Programme and of evaluating it using a randomised trial.

**Methods:**

This study is a feasibility cluster randomised controlled trial, with embedded process evaluation and health economic evaluation. Approximately 90 Year 5 (i.e. 9–10-year-old) girls will be recruited across six primary schools in Mid-South Wales. Participating schools will be allocated to the programme: control on a 2:1 basis; four intervention schools will run the CHARMING Programme and two will continue with usual practice. A survey and accelerometer will be administered at baseline and repeated at 12 months. Interviews and focus groups will be conducted post-intervention delivery. The primary aim is to assess feasibility of a future randomised trial via the recruitment of schools, participants and role models; randomisation; retention; reach; data collection completion rates; programme adherence; and programme fidelity, views on intervention acceptability and programme barriers and facilitators. Secondary aims are to evaluate established physical activity outcome measures for children plus additional health economic outcomes for inclusion in a future full-scale trial.

**Discussion:**

The results of this study will inform decisions on whether and how to proceed to a full-scale evaluation of the effectiveness and cost-effectiveness of the CHARMING Programme to improve or sustain physical activity.

**Trial registration:**

ClinicalTrials.gov ISRCTN36223327. Registered March 29, 2021

**Supplementary Information:**

The online version contains supplementary material available at 10.1186/s40814-021-00961-6.

## Background

Physical activity is important for young people’s health and wellbeing, but most young people are not active enough to encounter health benefits [1]. Young people in Wales are among the least active worldwide, with fewer than 20% of 11–16-year-olds meeting current guidelines of being active 60 min a day [2]. Studies show that girls tend to become less active than boys by age 10 and that this trend continues into secondary school [3]. There is a need for earlier intervention at primary school age, in the transition to adolescence, to prevent population level declines in girls’ physical activity through engaging less active girls in physical activity and maintaining activity levels among those who are already active [4].

Both social and physical environmental factors play a key role in increasing physical activity levels and understanding physical activity choices at the individual and contextual levels is a crucial step to informing the design of interventions aiming to increase physical activity [5]. As such, interventions grounded in a theoretical framework designed to influence such factors and choices may be more effective than those with no specified theory [6]. With differing mechanisms underlying physical activity levels and extracurricular physical activity playing a central part, there is a need to devise different types of intervention approaches for boys and girls aged 8–12 years [7]. Role models are a potential strategy to inspire young people to become involved, or maintain involvement, in physical activity and sport [8]. Adolescent girls were recently shown as more likely to be active if they had a role model who played sport compared to girls with role models who did not play sport [9]. Role models might positively influence behaviour by contributing, along with other factors, to the perception of specific behaviours (e.g. physical activity and sport participation) as attractive, attainable and rewarding experiences [10]. No one individual role model will be suitable for all young girls, but rather choices are made on the basis of exposure to family, peers and sports celebrities [8]. Such an intervention strategy has been internationally endorsed by the World Health Organization (WHO) with specific recommendations for the use of local community role models to increase physical activity among females [11]. The National Institute for Health and Care Excellence (NICE) also recommends that any practitioner leading physical activity initiatives, including teachers and volunteers, should provide appropriate role models [12]. Despite limited research and a lack of robust trials, policy recommendations strongly support the use of role models for tackling rising inactivity levels among girls [12, 13].

### Rationale and previous work

A formative study led by the Principal Investigator [14] adopted a participative community approach with key stakeholders to design and pilot a school-based role model intervention over a 12-month period. Framed by psychological and sociological theory, the intervention, CHARMING (CHoosing Active Role Models to INspire Girls), aims to promote key self-determination theory constructs and social ecological model constructs.

Main findings from this formative evaluation identified that (a) 28% of girls were unable to identify a role model for physical activity prior to the study pilot; (b) schools were a suitable location for the delivery of a community-linked role model programme; (c) role models and desired activities could be sourced from local communities; (d) intervention uptake and attendance was positive (46 out of 64 girls attended; of which 76% attended 5/6 sessions and 39% reported a black and minority ethnic background providing an early indicator that the intervention is unlikely to widen inequalities); (e) teachers perceived the intervention to be beneficial, highlighting increased opportunities for girls to be active, challenging gender norms in school and developing long-term community partnerships; and (f) recommended intervention modifications included; role model warm-up activities, a longer intervention delivery and the provision of consistent role models across sessions.

These results informed decisions on intervention refinement i.e. removing the warm-up activities, increasing the length of the intervention and adding a peer role model component. A lack of positive role models has previously been identified as a barrier to sport participation for girls [15] and data show that young girls in Wales are insufficiently active both on a national and global scale. Our earlier work [14] contributes to our understanding of the profile of physical activity role models of preadolescent girls (highlighting the importance of gender) and suggests potential for delivering a community-linked role-model programme in schools. Still, further work is required to understand the feasibility and acceptability of this on a larger scale with a demographically diverse population. Regarding the logistical considerations of sourcing peer role models, data suggests a greater influence when role models are relatable to the target audience [16]. Hence, prior to a trial of effectiveness, which may be undermined by difficulties sourcing role models or facilitating their attendance in the programme, or wider implementation issues [17], further feasibility testing is required to investigate these issues. In order to do this, and pilot the methods for a full-scale trial, this study will assess feasibility and acceptability of the CHARMING programme and its evaluation design.

The aim of the feasibility RCT is to assess the feasibility and acceptability of the CHARMING programme and proposed trial methodology. The study will aim to contribute to the evidence base on improving physical activity outcomes for 9–10-year-old girls. Importantly, the study will inform decisions on whether and how to proceed to a full-scale evaluation of the effectiveness and cost-effectiveness of CHARMING.

### Study objectives

The objectives of this study are as follows:Identify effective means of recruiting schools, participants and community and peer role modelsAssess the feasibility of conducting an effectiveness trial, economic evaluation and assess the implementation potential of the interventionExplore the acceptability of the intervention and the influence of school context on intervention implementationAssess the extent to which each of 6 progression criteria for conducting a full-scale trial are met

## Methods

### Trial design

This trial is a cluster randomised-controlled feasibility study, with allocation at the primary school–level and with an embedded process evaluation and health economic evaluation. Primary schools will be recruited and either randomised to run the intervention or continue with their usual practice.

This protocol was developed in line with the Standard Protocol Items: Recommendations for Interventional Trials (SPIRIT) guidelines; the SPIRIT checklist (Additional File 1) and the study schedule displayed in Table 1.

**Table 1 Tab1:**
[figure not shown]
SPIRIT protocol schedule for study timeline

### Study setting

Six secondary schools across Mid- and South Wales will be recruited into the study, with their adjoining primary schools invited to take part. The study flowchart can be seen in Fig. 1.

**Fig. 1 Fig1:**
[figure not shown]
Study flowchart

### Participants

Participants will be all year 5 girls (aged 9–10) who are opted-in by a parent (with written informed consent) and who provide their own assent.

### Eligibility criteria

Inclusion: All year 5 girls (aged 9–10) who are opted-in by a parent and who provide their own assent.

Exclusion: Children who cannot engage in physical activity due to medical reasons.

### Intervention—CHARMING Programme

The intervention is described using the TIDiER checklist (in Table 2). The intervention is a primary school-based physical activity programme, which consists of five planned components informed by psychological and sociological theory, integrating self-determination theory (SDT) [18] and the socio-ecological model [19]. As such the intervention programme focuses on (i) promoting children’s perceptions of autonomy, relatedness and competence in relation to physical activity and (ii) intrapersonal and interpersonal change within the school organisation and connections to the wider community and community opportunities for physical activity participation. The intervention has been designed to support physical activity engagement via three key psychosocial mechanisms: (1) giving girls the choice of which activities are delivered will support a sense of autonomy, (2) providing both community and peer-role models will increase the likelihood of relatedness and (3) providing a wide-range of activities will support perceived competence within a safe space among female peers. Along with enhanced enjoyment of physical activity, it is anticipated that these mechanisms will improve autonomous motivation, leading to greater maintenance of physical activity. Previous research has shown associations between psychological need satisfaction and autonomous motivation amongst the UK primary school age children [20].

**Table 2 Tab2:** Intervention description using the Template for Intervention Description and Replication (TIDieR) checklist

1. Brief name	CHoosing Active Role Models to INspire Girls (CHARMING)
2. Why	Less than a quarter of 11–16-year-olds meet current guidelines of being active 60 min a day. Girls are less active than boys and their physical activity levels drop quicker than male peers from the start of adolescence. The transition to adolescence is a crucial time to introduce approaches to support girls to become more active, and help stop the drop in physical activity among those who already are. The use of role models to promote physical activity has been recommended in international guidelines. Most similar studies have focused on older ages and are US-based. Better results have been shown among approaches that target girls only, are based in schools, include a range of activities, use theory and work with girls to produce a programme. A primary school-based role model programme, CHARMING, has been designed to increase and sustain physical activity levels among 9–11-year-old girls. The intervention is underpinned by psychological and sociological theory, integrating self-determination theory and the socio-ecological model.
3. What materials	Participants will have access to materials provided by the community role models following each session. Materials will signpost girls and parents to opportunities to continue the activity in their community using leaflets and usual school communication channels.
4. What procedures	Access to the intervention will be provided to schools upon randomisation to the intervention group. Schools receiving the intervention will run a 6-week programme consisting of five core planned components: 1-h taster physical activity sessions (1 per week after-school on school premises); community role model delivering the session, peer-role model(s) participating in each session, question and answer opportunity with role models post-session and sign-posting to community physical activity opportunities. All schools will have email access to the trial manager for any further enquiries. The linked secondary school recruits a group of secondary school students to act as ‘peer role models’ for the intervention [i.e. a females aged 11–16 years who young girls might look up to as a role model for physical activity] to participate in the weekly sessions in the primary school and support girls’ engagement with the intervention.
5. Who provided	The study manager will provide community role models and peer role models with a roles and responsibilities document. A recruitment poster will also be provided to the secondary school as a means of advertising the opportunity to be involved in the programme. The teacher will be fully responsible for recruiting and selecting peer role models to participate in the programme. Schools will be advised that the number of peer role models that can be involved is flexible and that this can depend on the level of interest in the opportunity, as well as current COVID-19 restrictions and bubbles. If fewer numbers are recruited all peer role models may wish to attend all sessions but in the event of several peer role models the school may wish to alternate attendance.
6. How	Primary schools will be notified by email upon randomisation to the intervention group and will gain access to the intervention manual along with a programme timetable and list of community contacts via the trial manager. Each school will oversee the timetable planning and subsequent delivery by community role models. Secondary schools will be notified as to whether their primary feeder school has been allocated to receive the intervention or control. In the event of intervention assignment, an introductory email will be sent to both the primary- and secondary lead teachers to formalise and facilitate the link for peer role model provision at each session. The community role model will be provided with the school’s contact details, address, session timings and approximate number of attendees by the study manager.
7. Where	Participants will access the intervention on the primary school premises.
8. When and how much	The programme will consist of a one-hour physical activity after-school session delivered each week for 6 weeks. There will be no cost to participate.
9. Tailoring	All participants will receive the same overarching programme structure; six 1-h sessions delivered over consecutive weeks on the school premises. In each intervention primary school, the local community physical activity provision is mapped to identify potential role models, and through communication with community providers and other physical activity stakeholders a timetable for the intervention is developed. This is done in collaboration with the school so that the interests and choices of the target population are taken into consideration when arranging the timetable.

The intervention logic model (see Additional File 2) displays the intervention planned components and how they link to the intended outcomes. In order to support organisation and delivery of the intervention, intervention manuals and guidelines are provided to the coordinating teacher in each primary and secondary school as well as the community and peer role models (see Additional File 3 for an overview of contents).

### Recruitment and consent

#### School recruitment and retention

State funded schools in South and Mid Wales, UK, will be invited to take part in the study. Six secondary schools will first be invited via the School Health Research Network (SHRN) and recruited to the study. These secondary schools will recruit secondary school students as peer role models to support intervention delivery in primary schools receiving the intervention. Each school will be asked to sign a memorandum of understanding to indicate their agreement to study participation. The memorandum will outline research processes and timelines, as well as roles and responsibilities.

For each secondary school, one feeder primary school will be purposively selected to ensure variation in socioeconomic status (percentage of students eligible for free-school meals), geographic location and school size and using publically available contact details, and invited to take part in the study. In the event that a school declines participation, a subsequent feeder school will be selected and invited to take part. An invitation to participate in the study will be sent to each secondary school’s feeder primary schools via email. A researcher will then contact schools by telephone to discuss the study. Following the same process for secondary schools, selected primary schools will also be asked to sign a memorandum of understanding. To maintain engagement, encourage retention and to thank schools for their time, they will be provided with quarterly newsletters from the time of allocation and a £200 donation following successful completion of the data collection activities. Schools will also receive a quarterly study newsletter, summarising study progress, in order to maintain school engagement, particularly for those schools allocated to control.

#### Child recruitment and parental consent

Two main forms of data collection will be conducted at baseline and again at a 12-month follow-up:A survey of self-reported outcome measuresCollection of 7-day accelerometry data (i.e. GT3X ActiGraph accelerometer, which is a non-invasive physical activity monitoring device worn on the waistband).

Recruited primary schools will be asked to invite all girls in year 5 (ages 9–10) to participate in the study at least 2 weeks prior to the data collection date. Year 5 girls will be provided with an information sheet, fully informing them of the study. Simultaneously, all the parents/carers of year 5 girls will be sent an electronic information sheet, fully informing them of the study and giving them the opportunity to opt their child in to the study. The information sheets will detail all possible aspects of their child’s participation in the study, including the completion of a short online survey in school and accelerometer and options of withdrawal up to the point of reporting; stating that children can participate in either the survey or accelerometer or both. The information sheet will highlight that the study is about evaluating an after school programme, but which schools are allocated to receive that or act as controls is down to chance. The information sheet will clearly state that their child can still take part in the after-school programme even if they do not participate in the study.

Parents/carers will be encouraged to discuss the information with their child prior to data collection. Parental written opt-in consent will be required for children to take part in the main trial components (survey and accelerometer). Parents/carers will be asked to return the opt-in form if they are happy for their child to participate in any aspect of the study. If a parent/carer does not return an opt-in form to the school by the 2-week deadline, their child will not enter the study. The class teacher will provide daily oral reminders to the children over this period to ensure that they and their parents read the information sheet and also utilise one other usual mechanism for communication (e.g. texts or emails home).

#### Child assent

All year 5 girls who have been opted in by parents/guardians and are in attendance on the day of data collection will be reminded of the research and their potential role in it. This will involve the teacher/online researcher reading a standardised script to the whole class, outlining all aspects pertaining to voluntary nature of the study, confidentiality and withdrawal. The script will also emphasise that pupils can still take part in the after school programme even if they do not take part in the study data collection. Teachers will be advised to distribute the activity monitors sensitively, being mindful of issues relating to body image and physicality. The research team will also provide the option for a researcher to virtually join (due to COVID-19) their data collection session through the use of an online video call.

To reiterate the study aims and assent process, the first page of the survey (whether electronic or paper-based) will include a simple information and assent section for year 5 girls. This will also outline all aspects pertaining to voluntary nature of the study, confidentiality and withdrawal. Information on how to complete the survey and skipping questions will be included. The child will be required to complete the assent statements for both the survey and activity monitor.

Pupils who have not been opted into the study by their parents, or who choose not to take part, will be provided with alternative activities by their teacher. This will also be the case for any boys within the year 5 classroom in the event that teachers need to keep the whole class together during data collection.

#### Sample size

As this study is focused on feasibility, the purpose is to provide estimates of key parameters for a future full-scale trial, rather than to power the current study to detect statistically significant differences. A total of 90 children within 6 recruited primary schools (allowing for an average of 15 girls in year 5) will allow an estimation of feasibility criteria with reasonable precision across a diverse range of context (e.g. intervention fidelity, completion of assessments, and valid primary outcome data). For girls within the intervention schools only (*n*=60), we will estimate that 50% will attend the intervention (i.e. minimum of one session) within ±12.7 percentage points using a 95% confidence interval. Similarly, for girls from all schools (*n*=90), the parameter of 70% returning valid primary outcome data can be estimated within ±9.5%, and 80% will complete baseline/follow-up to within ±8.3%.

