### Progression criteria for a potential future trial

Criteria for progression to a full-scale trial will be used to inform a decision on whether and how to proceed. Each progression criterion (PC) is outlined below.The intervention is implemented with fidelity (in a manner in line with intervention theory) in at least 3 of 4 intervention schools.At least 50% of assenting children in the intervention schools attend 50% of the scheduled sessions.The process evaluation indicates the intervention is acceptable to children, parents, school staff and role models.

Progression criteria relating to obtaining data regarding completion of outcome measures will be assessed using the following progression criteria:4.At least 3 of 4 intervention schools and 1 of 2 control schools are retained throughout the study. At least 80% of children approached complete the baseline and follow-up accelerometer measures. Proceed: 80% of children complete baseline and follow-up accelerometer measure; Stop: < 50%; Review: 50–79% of children complete.5.At least 70% of recruited children who receive an accelerometer return valid data (>3 days of 600 minutes including 1 weekend day) at baseline and follow-up for the primary outcome measure. Proceed: 70% or more; Stop: <40%; Review: 40–69%

These criteria have been agreed in advance of data collection with the Trial Steering Committee (TSC). The TSC will consider the quantitative and qualitative data [23] to review and make an overall judgement on whether the intervention can be delivered with fidelity. Potential impacts of COVID-19 will be considered as well as risk of generalisability bias [24]. In line with development guidance for feasibility studies [25], the study does not aim to provide an indication of the effectiveness of the intervention; given the small, purposively selected sample, such an estimate would not be meaningful.

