Accelerometry data will be analysed using a batch processing protocol; continuous periods of 60 min of zero counts will be considered as ‘non-wear time’ and removed. All data between 23:00 and 06:00 will be removed to ensure focus on awake time. Participants will be included in the analysis if they provide a minimum inclusion of 3 valid days. The percentage of original participants retained to 12-month follow-up who provide valid useable accelerometry data will be reported. Average counts per minute (CPM) will be used as a measure of total physical activity. Using the Evenson cut-points [28], the average daily minutes spent sedentary (cut-point of < 100 CPM), in MVPA (≥ 2296 CPM) and time-segment-specific time spent in each activity intensity (e.g. during club, after school or at weekends will be estimated using 7-day accelerometer data and summarised overall and by trial arm. Mixed-effects linear regression will be used to estimate direction of intervention effects on accelerometer-measured physical activity on the adjusted mean difference between intervention and control groups, alongside a 95% confidence interval (CI). School-level variance will be accounted for by inclusion of school as a random effect, and any remaining differences in the baseline assessment of the outcome measure, and local authority area (by which the randomisation was stratified), as fixed factors. The school-level intra-class correlation (ICC) coefficient for average daily minutes of MVPA over the 7 days will be estimated alongside a 95% CI. Whilst likely non-significant due to limited power, this should be in the direction of a favourable intervention effect.

Response rates and level of completion of the survey measures such as (self-reported physical activity (PAQ-C scale), psychosocial outcomes (activity-based perceptions of autonomy, relatedness, competence and enjoyment) and current after-school sport or physical activity club attendance (school and community), at baseline and 12-month follow-up will be reported using descriptive statistics. Regression models will also be used to estimate direction of intervention effects on 12-month survey outcomes. Mixed-effect models will take the clustering of individuals in schools into account using a random model and adjust for baseline outcomes.

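### The three precisions in the sample size section (±12.7, ±9.5 and ±8.3 points) are simple binomial values that ignore clustering by school, so they are too narrow for any positive school ICC

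*Protocol article*

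**What the plan says.** The Sample size section sets the numbers as "A total of 90 children within 6 recruited primary schools (allowing for an average of 15 girls in year 5"), and says that this "will allow an estimation of feasibility criteria with reasonable precision across a diverse range of context". It then gives three 95% half-widths:

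- Attendance, on the 60 girls expected in the four intervention schools: "we will estimate that 50% will attend the intervention (i.e. minimum of one session) within ±12.7 percentage points using a 95% confidence interval".
- Valid accelerometer data, all 90 girls: "the parameter of 70% returning valid primary outcome data can be estimated within ±9.5" points.
- Completion, all 90 girls: "80% will complete baseline/follow-up to within ±8.3" points.

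The section mentions no ICC, design effect or other allowance for schools. Elsewhere the article does allow for clustering. Under Statistical analysis, for the accelerometer outcome, "School-level variance will be accounted for by inclusion of school as a random effect", and the survey models also take clustering into account. Under Economic analysis, response and completion rates for the two quality-of-life measures are to be described with clustering taken into account.

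**The concern.** Girls in one school share a teacher, a timetable, role models and a teacher-led data collection, so attendance, valid wear and completion are likely to be more alike within a school than between schools. The fourth progression criterion shows how this can happen: it tolerates losing one of the four intervention schools. At 15 girls each, one lost school takes away 15/90 = 16.7 percentage points of completion at a stroke, twice the stated ±8.3.

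The article is also inconsistent with itself. It takes clustering into account when describing completion of the economic measures, but gives the precision of the same kind of rate as though girls were independent.

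At stake is the accuracy of the stated justification. These half-widths are the only quantitative support for the sample size, and they are computed at 50%, 70% and 80%, the same percentages as the thresholds in the progression criteria.

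**Working it through.** **Inputs from the article.** 6 schools, 4 of them intervention; an average of 15 girls per school; n = 60 (4 × 15) and n = 90 (6 × 15); proportions 0.50, 0.70 and 0.80; 95% confidence.

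**Assumed input.** The school ICC, shown as a range because the article gives no value for any of these proportions.

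**Step 1: reproduce the stated figures.** Half-width = 1.96 × √(p(1−p)/n).

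- Attendance: 1.96 × √(0.25/60) = 12.65, stated 12.7
- Valid data: 1.96 × √(0.21/90) = 9.47, stated 9.5
- Completion: 1.96 × √(0.16/90) = 8.26, stated 8.3

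Other unclustered intervals do not give all three: Wilson gives 12.3, 9.3 and 8.2; Clopper–Pearson 13.2, 9.9 and 8.7; Agresti–Coull 12.3, 9.3 and 8.3. The figures are therefore Wald intervals with a design effect of 1. The arithmetic is right; the independence assumption is what fails.

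**Step 2: allow for clustering.** Design effect = 1 + (15 − 1) × ICC. Each half-width is multiplied by √(design effect), and the effective n is n divided by the design effect.

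| Assumed ICC | Design effect | Effective n (of 60; of 90) | 50% of 60 | 70% of 90 | 80% of 90 |
|---|---|---|---|---|---|
| 0 (as stated) | 1.00 | 60; 90 | ±12.7 | ±9.5 | ±8.3 |
| 0.01 | 1.14 | 52.6; 78.9 | ±13.5 | ±10.1 | ±8.8 |
| 0.02 | 1.28 | 46.9; 70.3 | ±14.3 | ±10.7 | ±9.3 |
| 0.05 | 1.70 | 35.3; 52.9 | ±16.5 | ±12.3 | ±10.8 |
| 0.10 | 2.40 | 25.0; 37.5 | ±19.6 | ±14.7 | ±12.8 |
| 0.20 | 3.80 | 15.8; 23.7 | ±24.7 | ±18.5 | ±16.1 |

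Example at ICC 0.05: 12.65 × √1.70 = 16.5.

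**Step 3: few schools.** The table keeps the normal multiplier of 1.96. If the between-school variation has to be estimated from the 4 or 6 schools themselves, a t multiplier with 3 or 5 degrees of freedom applies. At ICC 0.05 that gives about ±26.8, ±16.2 and ±14.1.

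**The case against.** The strongest reply is that this is a feasibility trial, that its feasibility analysis is described as mainly descriptive, and that the steering committee weighs quantitative and qualitative evidence in an overall judgement, so no decision hangs on these intervals. The ICC is also unknown, and at 0.01 the loss is under one point on each figure. All of this stands. It limits the importance of the point, but a published precision that holds only at zero ICC is still misstated.

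The same reasoning rules out four stronger readings that a reader might infer.

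- **That progression bands can no longer be separated.** The planned 70% and 80% lie on the Proceed thresholds, so even ±9.5 and ±8.3 could not separate Proceed from Review there. The Stop limits (below 40% and below 50%) are 30 points lower. At ICC 0.20 the half-widths are ±18.5 and ±16.1, or about ±24.2 and ±21.1 with the t multiplier, and neither reaches 30. The attendance criterion has no Review or Stop band. The article claims only reasonable precision.
- **That the plan assumes every Year 5 girl is recruited.** The wording allows this, but 15 per school may equally mean girls recruited; the Abstract speaks of recruiting approximately 90. It is an ambiguity, not a demonstrated error. The completion criterion is also counted per child approached, so incomplete opt-in need not reduce its n.
- **That the formative uptake (46/64, 72%) predicts consent.** That figure is programme attendance. The article says girls may attend the programme without joining the study, so it is no basis for an opt-in rate.
- **That the attendance precision is given for the wrong parameter.** The progression criterion reads "At least 50% of assenting children in the intervention schools attend 50% of the scheduled sessions", whereas the sample size section uses at least one session. At 50% of 60 girls the half-width is the same for either event, and attending at least one session is itself a planned reach measure under Statistical analysis.

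**Conclusion.** The point holds as a correction to the stated precision. The three half-widths are unclustered values, and no part of the article supplies a design effect. They are too narrow for any positive school ICC: by less than one point at 0.01, by about 2.5 to 4 points at 0.05 (8.3 to 10.8; 12.7 to 16.5), and by about 4.5 to 7 points at 0.10 (8.3 to 12.8; 12.7 to 19.6), before any allowance for the small number of schools.

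These sizes rest on assumed ICCs and on 15 analysed girls in every school. The direction does not depend on which positive ICC is chosen. The point does not show that the trial is too small for its purpose or that a progression decision would change. It is a modest correction of wording and reporting.

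**What to change.** 1. In the sample size section, restate the half-widths with a design effect of 1 + (15 − 1) × ICC over a declared ICC range, for example ±13.5, ±10.1 and ±8.8 at 0.01; ±16.5, ±12.3 and ±10.8 at 0.05; ±19.6, ±14.7 and ±12.8 at 0.10. Add that having only four or six schools widens them further. Alternatively, keep the current figures and label them an unclustered best case.
2. State whether 15 per school means Year 5 girls on roll or girls recruited after parental opt-in and assent. If it means girls on roll, give the opt-in rate assumed.
3. Report the observed progression rates with cluster-adjusted 95% confidence intervals, in line with what is already planned for completion of the economic measures.

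The cost is a less favourable stated precision and slightly more work in reporting. No further schools or girls are needed.
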